# Protocol Synopsis

## Title of study

CytoResc - CytoSorb Rescue for COVID-19 Cytokine Storm

## Study design:

Multicenter, prospective, open-label, randomized pilotstudy investigating the effect of the use of CytoSorb in patients with vasoplegic shock due to suspected cytokine storm in patients with COVID-19.

## **Study centers**

Approximately 5 sites in Germany with approximately 10 Intensive Care Units (ICU)

## Study Product

CytoSorb (Cytosorbents, Corporation, New Jersey, USA) is a hemoadsorption device containing hemocompatible, porous polymer beads capable of removing cytokines and other medium molecular weight toxins from the blood by size exclusion and surface adsorption. The polymer is both highly adsorptive and biocompatible and has been CE certified in the European Union. Only CE-certified medical devices are used in the study according to their indications. Certificates/Instructions for use are attached

### Reference exposure

Standard treatment without CytoSorb

### Investigational exposure

CytoSorb treatment for 3-7 days initiated within 24 hours after fullfilling the inclusion criteria

## Study period

Cytosorb treatment for 3-7 days

Patient inclusion over 8 weeks

## Study purpose

To evaluate the effect of extracorporeal cytokine elimination with CytoSorb treatment in critically ill COVID-19 patients with suspected cytokine storm.

## **Methods**

This is a randomized, prospective, open-label, multicenter trial investigating the effect of the use of CytoSorb in patients with vasoplegic shock due to suspected cytokine storm in patients with COVID-19. Patients with vasoplegic shock as an indicator of suspected cytokine storm will be randomized to receive either standard of care of standard of care and additional CytoSorb therapy for 3-7 days. Measurement of Interleukin-6 is done on day 1 and 3 respectively.

## Objectives and Outcome measures

### Primary efficacy endpoint:

- time until resolution of vasoplegic shock (defined as no need for vasopressors for at least 8 hours in order to sustain a MAD ≥ 65mmHg) in days

### Secondary endpoints:

- 7 day mortality after fulfilling the inclusion criteria
- mortality until hospital discharge
- measurement of IL-6 on day 1 and 3 of intervention
- need for mechanical ventilation
- duration of mechanical ventilation
- duration of ICU-stay
- catecholamine dose on day 1/2/3 after start of CytoSorb
- acute kidney injury

## Population

The study population will consist of critically ill COVID-19 patients who are consecutively admitted to the ICU of the participating centers and fulfilling the inclusion criteria.

## Inclusion/Exclusion criteria

### Inclusion criteria:

- Males or females aged 18-80 years
- Positive PCR test for SARS-CoV-2
- Vasoplegic shock (Noradrenalin > 0.2 µg/min/kg (aiming MAD ≥ 65mmHg))
- CRP > 100 mg/l
- PCT < 2 ng/l

### Exclusion criteria:

- Patients receiving Tocilizumab (anti-IL6-receptor antibody)
- Patients not applicable for anticoagulation (if Heparin is not applicable local anticoagulation with citrate or systemic Argatroban can be used, severe thrombocytopenia < 20.000/μl is a contraindication
- pregnancy
- bacterial infection

## Safety assessment

CytoSorb is a medical device which is already well implemented in routine clinical practice and CE-certified in the European Union. Several clinical studies and a large registry have not shown any serious side effects. It can be assumed that this can also be transferred to the study participants. The medical device is used within the scope of its approval.

However, in order to exclude risks for the study participants a safety surveillance system will be established including ongoing reports on serious adverse events and mortality sent to the investigators. After each 20 patients an independent Data Safety Monitoring Board (DSMB) will review the safety data of the trial. (see point 5 for details).

## Data assessment and Data analysis

Data capture and data management will be performed using electronic case report forms (eCRF) based on the study software secuTrial^®^ which is provided by the Clinical Study Center (CSC) Charité. Statistical analysis and report writing will be performed when all patients have left the study. Data on mortality and serious adverse events are monitored continuously. (see point 5.)

## Sample size

Not applicable as the study serves as a pilotstudy. Possibly 85-100 patients

# Introduction

Until April 23rd, 2020, 2.640.000 people were tested positive for COVID-19 worldwide. (1, 2) Mortality rates are between 0,7-7%, with variations probably due to different cohorts, different capacities of the health care systems and most likely other unknown factors. Approximately 14 % of the infected patients present with a serious clinical course; 5% need ICU-treatment.(3) This is stretching medical systems around the world to the limit of their capacity and might lead to several non-evidence-based medical treatments. In fact, some organizations are already giving advice to use investigative treatment as compassionate use in COVID-19 patients. Some of those are not without risk. (4)

Until now, treatment is purely supportive. The main cause of death in critically ill patients is acute respiratory failure. (3) There are several observations indicating a cytokine storm leading to acute decompensation of patients which might be a possible option for therapeutic intervention.(5, 6) Several possible treatment options are discussed including streroids, Tocilizumab (an anti-IL6-receptor antibody) as well as extracorporeal elimination. So far, there is no evidence for any of them. On the contrary, steroids and Tocilizumab may even be harmful due to immunosuppression. A recent paper, currently under review for publication in CELL-HOST-MICROBE actually found the expression of proinflammatory genes, especially chemokines, to be markedly elevated in bronchoalveolar lavage fluid of COVID-19 patients as compared to patients with community-aquired pneumonia patients and healthy controls, suggesting that SARS-CoV-2 infection causes hypercytokinemia. (7)

The fact, that multiple chemokines were elevated supports the use of a broader therapy such as extracorporeal cytokine elimination as compared to e.g. Tocilizumab as anti-IL6-receptor antibody.

CytoSorb is an adsorber containing hemocompatible, porous polymere chains, which are able to eliminate cytokines and other toxins of middle molecular weight from the blood. The polymer is highly adsorptive as well as biocompatible and was CE-certified in the European Union.

We hypothesized that the elimination of cytokines might improve outcome in critically ill COVID-19 patients with suspected cytokine storm. As primary endpoint we decided on the time until resolution of vasoplegic shock, a well implemented, clinically relevant endpoint in critical care studies. (8, 9)

Several preclinical studies in animal models showed a reduction of different cytokines and chemokines.(10, 11) Data on clinical effectiveness is inconsistent. In a prospective study in sepsis patients no significant reduction of circulating IL-6 could be detected, however, this might have been due to a heterogeneous patient cohort. (12) Data from an international register suggest clinical effectiveness as well as adequate reduction of cytokine-elimination in a big cohort. (13) In fact, recent data show the succesfull use of CytoSorb in CAR-T-associated cytokinestorm. (14) Despite inconsistent clinical evidence CytoSorb is already broadly used in critically ill patients with sepsis. (13, 15) Apart from the invasiveness of the procedure (there is the need for a big central venous access that most critical patients have anyway) the method is known to be safe. (12, 13, 16)

In order to build prospective reliable evidence (also including negative results) we are planning to do a pragmatic randomized-controlled open-label pilotstudy. The aim of this study is to investigate the effect of the use of CytoSorb in order to eliminate cytokines in critically ill patients with COVID-19.

# Study design

Multicenter, prospective, open-label, randomized pilotstudy investigating the effect of the use of CytoSorb in patients with vasoplegic shock due to suspected cytokine storm in patients with COVID-19. We will consecutively include all eligible patients during a timeframe of eight weeks and randomize them to receive either CytoSorb treatment or standard of care without CytoSorb to eventually plan an adequately powered randomized controlled trial with sample size calculation as a subsequent trial. Study centers will be approximately 5 sites in Germany with approximately 10 Intensive Care Units (ICU). We are assuming an inclusion rate of possibly 85-100 patients.

## Intervention scheme

All patients aged 18-80 tested positive for SARS-CoV-2 via PCR and presenting with vasoplegic shock (defined as need for noradrenaline > 0.2 µg/min/kg (MAD aim ≥ 65mmHg) with infection markers implying a non-bacterial genesis (CRP > 100 mg/l, PCT < 2 ng/l) are eligible for the study. After written informed consent randomization is done using an electronic data system to either receive standard of care with or without CytoSorb treatment. Therapy is done open-label as blinding is not feasible. If not already implemented, patients in the intervention group receive a shaldon catheter after appropriate education. To avoid unnecessary risk of complications, the catheter is inserted by an experienced medical doctor. The intervention is done for 3-7 days irrespectively of indication to renal replacement therapy. Filter exchange is done every 24 hours. If the patient is receiving antibiotics an additional dose is given after every filter exchange in order to control for underdosage. Measurements of IL-6 are done on day 1 and 3 respectively. Primary endpoint is time to resolution of vasoplegic shock. Predefined routine clinical data which serves as outcome variables as well as adverse events are documented in an electronic data base using an eCRF.

Figure 1: Trial Flow Chart

## Study Endpoints

### Primary efficacy endpoint:

- time until resolution of vasoplegic shock (defined as no need for vasopressors for at least 8 hours in order to sustain a MAD ≥ 65mmHg) in days

### Secondary Endpoints:

- 7 day mortality after fulfilling the inclusion criteria
- mortality until hospital discharge
- measurement of IL-6 on day 1 and 3 of intervention
- need for mechanical ventilation
- duration of mechanical ventilation
- duration of ICU-stay
- catecholamine dose on day 1/2/3 after start of CytoSorb
- acute kidney injury

As primary endpoint we decided on the time until resolution of vasoplegic shock, a well implemented, clinically relevant endpoint in critical care. Two big intensive care studies already used this endpoint as secondary endpoint. (8, 9)

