# Study assessment

All laboratory determinations including will be analyzed locally.

Baseline variables:

- Age
- Sex
- Smoker status
- Comorbidities
  - Hypertension
  - Diabetes
  - Coronary heart disease
  - COPD
  - History of malignancy
  - Chronic kidney disease
  - Immunosuppression
  - Other

At inclusion

- Oxygen supplementation
- NIV/High Flow
- Intubation
- ECMO
- Vasoplegic shock
- Dose of Noradrenaline
- Other Vasopressors
- Glucocorticoids
- Antiviral treatment
- SOFA
- APACHE

Outcome parameters

- Time to resolution of shock (d)
- Need for mechanical ventilation
- Days on ventilator after inclusion (d)
- ICU survival
- In-hospital mortality
- 7 day mortality
- Septic shock
- Cardiogenic shock
- Acute kidney injury after Inclusion (AKIN-Stage 1,2,3)
- Dialysis
- Duration of ICU stay
- Vasopressor dose (max) on day 1
- Vasopressor dose (max) on day 2
- Vasopressor dose (max) on day 3
- Change to palliative therapy

Adverse events

- technical failure
- mashine clotting
- other

Serious adverse events

- Cardiac arrest
- Severe bleeding
- Severe allergic reaction
- Severe Complication due to shaldon catheter insertion
- Death
- Other

Complication possibly associated with CytoSorb

- Heparin induced thrombycytopenia Type 2 (HIT 2) if heparine is exclusively needed for CytoSorb therapy
- Complication associated with shaldon catheter insertion if catheter is exclusively needed for CytoSorb therapy
- Severe allergic reaction associated with CytoSorb therapy
- Other

Laboratory Data (day 1+3+7)

- CRP
- Troponin
- D-Dimer
- IL-6 (Only Day 1+3)
- Ferritin
- LDH
- Creatinine
- ALT
- PCT
- Phosphate

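### Two of the eight secondary endpoints, catecholamine dose and IL-6, are timed from an event that only the CytoSorb arm has

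*Protocol*

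**What the plan says.** The secondary endpoints appear twice in the protocol, in the synopsis and under Study Endpoints, with the same wording. Two of the eight are counted from treatment: "catecholamine dose on day 1/2/3 after start of CytoSorb" and "measurement of IL-6 on day 1 and 3 of intervention". A third names a different origin: "7 day mortality after fulfilling the inclusion criteria".

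The comparator, under Reference exposure, is "Standard treatment without CytoSorb". Under Investigational exposure, the device is to be "initiated within 24 hours after fullfilling the inclusion criteria".

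The data list under Study assessment carries the corresponding variables as "Vasopressor dose (max) on day 1" (with matching entries for days 2 and 3) and "IL-6 (Only Day 1+3". Neither entry says what the day is counted from, and neither is limited to one arm. In the same list, ventilator days and acute kidney injury are counted after inclusion. The Methods and Intervention scheme sections also give IL-6 by day number only. Statistical analysis says that secondary endpoints will be evaluated with a proportional hazards model, ANCOVA or logistic regression, chosen by distribution. It names no time origin for them.

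**The concern.** A between-arm comparison needs a time zero that every randomised patient has. Start of CytoSorb occurs after randomisation and in one arm only. If it defines the day count, two things follow.

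First, a site or analyst has to invent a day 1 for controls. The natural choice, inclusion, can differ from filter start by up to a day. In patients whose vasopressor need and IL-6 may be changing quickly, reading one arm later than the other creates a difference that has nothing to do with the device.

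Second, a patient assigned to CytoSorb who never starts it, for instance because of early death, has no value on this clock. No control can drop out for that reason, so the comparison is no longer as randomised.

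The pilot is meant to inform the effect size for a later trial, and IL-6 is the most direct measure of the cytokine-removal rationale. A blood sample drawn at the wrong time cannot be corrected at analysis.

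**Working it through.** The protocol gives no figure to reproduce here: sample size is declared not applicable, and no effect size is stated. The check has two parts.

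**1. Time origins side by side**

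| Item | Origin stated | Exists in controls? |
|---|---|---|
| 7-day mortality | Fulfilling the inclusion criteria | Yes |
| Ventilator days, acute kidney injury (Study assessment) | Inclusion | Yes |
| Catecholamine dose, days 1/2/3 (endpoint lists) | Start of CytoSorb | No |
| IL-6, days 1 and 3 (endpoint lists) | Day of intervention | No |
| Vasopressor dose and IL-6 (Study assessment) | None given | Not determined |

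Start of CytoSorb is not simply another name for inclusion or randomisation. The Intervention scheme places consent, randomisation and, where needed, catheter insertion before it, and the permitted interval from eligibility is 0 to 24 hours.

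**2. Illustration of what a mixed clock would do**

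Assumptions, none of them from the protocol:
- there is no treatment effect;
- dose falls by a fraction d per day, with d = 0.10, 0.20 or 0.30;
- controls are counted from inclusion, and CytoSorb patients from filter start, L days later.

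For a fixed lag, the CytoSorb/control dose ratio is (1 − d)^L. At L = 1 (24 hours):
- d = 0.10: 0.90
- d = 0.20: 0.80
- d = 0.30: 0.70

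For a lag spread evenly over 0-24 hours, the mean ratio is the integral of (1 − d)^u for u from 0 to 1, which equals d / (−ln(1 − d)):
- d = 0.10: 0.10 / 0.1054 = 0.95
- d = 0.20: 0.20 / 0.2231 = 0.90
- d = 0.30: 0.30 / 0.3567 = 0.84

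To set this against sampling error, take 42-50 patients per arm. That is the protocol's possible 85-100 halved; 1:1 allocation is a further assumption. Take an assumed SD of log dose of 0.5 to 0.8. With δ = −L·ln(1 − d) and SE = SD·√(2/n), the two-sided 5% rejection rate under no effect is Φ(δ/SE − 1.96) + Φ(−δ/SE − 1.96).
- Smallest case at 24 hours (n = 42, SD 0.8, d = 0.10): δ = 0.105, SE = 0.175, rate about 9%.
- Largest case at 24 hours (n = 50, SD 0.5, d = 0.30): δ = 0.357, SE = 0.100, rate about 95%.
- At a 12-hour lag, the range is about 6% to 43%.

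The width of these ranges shows how far the result depends on the assumptions. With one origin shared by both arms, L = 0, the ratio is 1.00 and the rate is the nominal 5%.

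**The case against.** The strongest reply is that the data list under Study assessment records vasopressor dose and IL-6 by plain day number, without restriction by arm and without mention of CytoSorb, and that neighbouring items run from inclusion. If sites count those days from a common point, the data are comparable and the bias is zero. The flow chart is not reproduced and the SAP is not at hand; either may number the days. The analyses are declared explorative, and the primary endpoint is not tied to filter start.

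Most of this stands, and it limits the point. It does not remove it: the endpoint definitions, given twice, name an origin that controls lack, and the data list supplies no other. This is an origin stated wrongly, not a detail left for the SAP.

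A reader might infer more than the protocol supports:

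- **That the arms cannot be compared at all.** This is true of the two definitions as worded, but not of the variables collected.
- **That the bias favours CytoSorb.** This needs controls counted from inclusion, which the protocol does not state, and falling values. With rising values the direction reverses.
- **That 9-16% of CytoSorb patients would lack a value.** This comes from assuming a median of 7 or 4 days to resolution or death with a constant hazard: 1 − 2^(−1/7) = 9.4% and 1 − 2^(−1/4) = 15.9%. The median is not in the protocol, and the calculation supposes that every patient starts at the 24-hour limit. It also counts resolved patients as missing, although their dose is recordable as zero.
- **That adjusting for day-1 IL-6 removes part of the effect.** The protocol lists ANCOVA only as one possible model and does not name day-1 IL-6 as a covariate.

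**Conclusion.** The concern holds for two of the eight secondary endpoints: catecholamine dose and IL-6. Their stated origin exists only in the CytoSorb arm. Read literally, they leave controls without a day 1 and leave patients who were assigned to CytoSorb but never started it without a value.

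The distortion is bounded by the permitted 24 hours, so it is at most about one day on a three-day endpoint. It arises only if the arms are in fact counted from different points. The ratios shown (0.90-0.70 at the full lag, 0.95-0.84 with an even spread) rest on an assumed daily fall in dose and are not forecasts for this trial.

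This should be fixed, but it does not put the trial's main result in doubt: the endpoints are secondary, the study is an exploratory pilot, and the primary endpoint and the other six secondary endpoints do not depend on filter start.

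**What to change.** - Define day 1 once, for both arms, from the date and time of randomisation, and state in hours what each day number covers.
- Restate the two endpoints as vasopressor dose on days 1, 2 and 3, and IL-6 on days 1 and 3, after randomisation.
- Use the same definition in the synopsis, under Study Endpoints and in the Study assessment list.
- Analyse all patients in the arm to which they were randomised, whether or not the filter was started.
- Record the time of filter start and the time of the day-1 IL-6 sample, so that it is known whether the sample preceded the filter. Use that value as a baseline covariate only if it was drawn before filter start.

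The other endpoints need no new time zero on account of this point. The cost is endpoint wording and date/time fields in the eCRF.

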## Randomization

An electronic randomization will be performed using the study software secuTrial^®^ admistered by the Clinical Study Center (CSC) of the Charité.

## Blinding assessment

Blinding is not feasible as a clinical intervention is done. The intensive care unit where the patient is treated will be added as random effect in the model in order to control for cluster effects. The statistician will be blinded.

# Study assessment

All laboratory determinations including will be analyzed locally.

Baseline variables:

- Age
- Sex
- Smoker status
- Comorbidities
  - Hypertension
  - Diabetes
  - Coronary heart disease
  - COPD
  - History of malignancy
  - Chronic kidney disease
  - Immunosuppression
  - Other

At inclusion

- Oxygen supplementation
- NIV/High Flow
- Intubation
- ECMO
- Vasoplegic shock
- Dose of Noradrenaline
- Other Vasopressors
- Glucocorticoids
- Antiviral treatment
- SOFA
- APACHE

Outcome parameters

- Time to resolution of shock (d)
- Need for mechanical ventilation
- Days on ventilator after inclusion (d)
- ICU survival
- In-hospital mortality
- 7 day mortality
- Septic shock
- Cardiogenic shock
- Acute kidney injury after Inclusion (AKIN-Stage 1,2,3)
- Dialysis
- Duration of ICU stay
- Vasopressor dose (max) on day 1
- Vasopressor dose (max) on day 2
- Vasopressor dose (max) on day 3
- Change to palliative therapy

Adverse events

- technical failure
- mashine clotting
- other

Serious adverse events

- Cardiac arrest
- Severe bleeding
- Severe allergic reaction
- Severe Complication due to shaldon catheter insertion
- Death
- Other

Complication possibly associated with CytoSorb

- Heparin induced thrombycytopenia Type 2 (HIT 2) if heparine is exclusively needed for CytoSorb therapy
- Complication associated with shaldon catheter insertion if catheter is exclusively needed for CytoSorb therapy
- Severe allergic reaction associated with CytoSorb therapy
- Other

Laboratory Data (day 1+3+7)

- CRP
- Troponin
- D-Dimer
- IL-6 (Only Day 1+3)
- Ferritin
- LDH
- Creatinine
- ALT
- PCT
- Phosphate

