# Statistical analysis

A recent retrospective observational study showed a mortality of 61.5% in a cohort of 52 critically ill COVID-19 patients. (18) Due to both the explorative character of the study (new virus, heterogeneous data on efficacy of CytoSorb-treatment in general an no data in COVID-19-patients at all) and few data on possible recruiting rates (patient flow not estimable, patient condition not estimable) we cannot make assumptions on the effect size of the intervention. That is why, supported by the Institute of Biometry and Clinical Epidemiology of the Charité, we decided on an investigator-initiated clinical pilotstudy in order to evaluate the feasibility of recruitment and gain knowledge concerning the intervention effect. We will consecutively include all eligible patients for a period of eight weeks and randomize them to either receive CytoSorb treatment or standard of care without CytoSorb in order to plan an adequately powered randomized controlled trial with the gained knowledge on effect size and recruitment feasibility as a subsequent trial.

The primary analysis in order to evaluate the effect of the intervention will be carried out with a shared frailty model with time until resolution of vasoplegic shock as outcome variable censored at the time of death. The randomization group will be included as fixed effect and additionally possible confounder such as age, sex and pre-existing illness.

The intensive care unit where the patient is treated will be added as random effect in the model in order to control for cluster effects.

As an additional analysis, death will be treated as competing risk, results will be shown in a cumulative incidence function.

Secondary endpoints will be evaluated with adequate models (proportional hazards model / ANCOVA / logistic regression) depending on distribution of endpoint variables.

All the analyses will be explorative and will not be controlled for multiple testing. Since missing data is not expected, imputation is not planned.

Blinding of the investigator and patient is not possible as a clinical intervention is done, statistician will receive a blinded data set, so that all analyses will be conducted blinded.

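### AKIN stage and ongoing renal replacement are not listed for recording at inclusion, so new dialysis cannot be told from existing dialysis and new kidney injury rests on unchecked judgement

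*Protocol*

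**What the plan says.** **Outcome.** The protocol's Secondary Endpoints list (and the matching list in the Synopsis) gives only "acute kidney injury", with no reference to inclusion. Among the outcome parameters, the Study assessment section is more specific: "Acute kidney injury after Inclusion (AKIN-Stage 1,2,3". Dialysis is a separate outcome item there, with no statement that it must be newly started.

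**Recorded at inclusion.** The same section lists respiratory support, ECMO, shock, noradrenaline dose, other vasopressors, glucocorticoids, antiviral treatment, SOFA and APACHE. AKIN stage and renal replacement are not on the list.

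**Other kidney information.** "Chronic kidney disease" is a baseline comorbidity. Creatinine falls under "Laboratory Data (day 1+3+7". No pre-illness creatinine and no urine output are listed, and SOFA and APACHE appear without their components.

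**Who may enter.** The exclusion criteria name neither acute kidney injury nor dialysis. The Intervention scheme says: "The intervention is done for 3-7 days irrespectively of indication to renal replacement therapy".

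**Analysis.** On size the protocol says "We are assuming an inclusion rate of possibly 85-100 patients"; on effect, "we cannot make assumptions on the effect size of the intervention"; on inference, "All the analyses will be explorative and will not be controlled for multiple testing".

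**The concern.** An outcome counted from inclusion onwards needs the state at inclusion. The protocol follows this logic for the lungs: need for mechanical ventilation is an endpoint, and intubation is recorded at entry. It does not do so for the kidney.

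All patients enter in vasopressor-dependent shock, so some may already have kidney injury or be on renal replacement. A patient on dialysis at entry will also be on dialysis afterwards, and the listed items cannot show which came first. A patient already at AKIN stage 3 cannot move up the scale, and one at stage 1 or 2 may or may not be scored as a case, because no rule is given. Open-label investigators in about ten intensive care units would each decide, and the database could not check them.

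What is at stake is whether two kidney outcomes can be interpreted in a pilot meant to inform a later trial. A statistical analysis plan can define an at-risk set, but it cannot supply an entry value that was not collected.

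**Working it through.** **No figure to reproduce.** The protocol gives no rate, event count or power for kidney injury. The check therefore compares the data items, followed by an illustration on assumed rates.

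**Step 1: what the listed items can establish**

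| Item listed | On renal replacement at entry? | AKIN stage at entry? |
|---|---|---|
| Chronic kidney disease | No | No (chronic, not acute) |
| SOFA, APACHE (components not named) | No | No |
| Creatinine, day 1 | No (renal replacement itself lowers it) | No (no reference value, no urine output) |
| Creatinine, days 1, 3, 7 | No | No, but shows a later rise in patients not on dialysis |

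Entry renal function can be partly described and adjusted for. Entry dialysis cannot be identified.

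**Step 2: effect of counting entry cases as events**

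Let f be the share already affected at entry, equal in both arms, and let p_C and p_T be the rates of new injury among those at risk.

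- Observed rate in an arm: f + (1 − f)p
- Observed risk difference: (1 − f)(p_C − p_T)

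Assumptions, none from the protocol: p_C = 0.40, p_T = 0.20; 1:1 allocation (inferred from the safety reviews at 10 per group, or 20 patients); two-sided 5% level; pooled two-proportion power formula. N = 85 and 100 are the protocol's recruitment range. The last two columns restrict the analysis to the (1 − f)N patients at risk.

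| f | Rates observed | Difference | Risk ratio | Power, all (N = 100) | Power, all (N = 85) | Power, at risk (N = 100) | Power, at risk (N = 85) |
|---|---|---|---|---|---|---|---|
| 0 | 0.40 v 0.20 | 0.20 | 0.50 | 59.0% | 52.1% | 59.0% | 52.1% |
| 0.2 | 0.52 v 0.36 | 0.16 | 0.69 | 36.2% | 31.5% | 49.7% | 43.5% |
| 0.4 | 0.64 v 0.52 | 0.12 | 0.81 | 22.7% | 19.9% | 39.1% | 34.0% |

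For f = 0.4: 0.4 + 0.6 × 0.40 = 0.64 and 0.4 + 0.6 × 0.20 = 0.52, so the difference is 0.12.

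With assumed rates of 50% and 30% and N = 100, power is 35.8% (all) against 44.5% (at risk) at f = 0.2, and 23.7% against 34.9% at f = 0.4.

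**Step 3: entry cases scored as non-events instead**

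The arm rates become (1 − f)p. The risk difference shrinks by the same factor, but the risk ratio stays at 0.50. With 40% v 20%, N = 100 and f = 0.4, the rates are 0.24 and 0.12, and power is 34.3%.

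**Step 4: chance imbalance in f**

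If the arms differ in f by δ and treatment does nothing, entry cases counted as events give a difference of δ(1 − p). With 50 per arm and f = 0.4, the standard error of δ is √(2 × 0.4 × 0.6 / 50) = 0.098. Taking p = 0.3, an imbalance of one standard error moves the difference by 0.098 × 0.7 = 0.069, about 7 points, in either direction. An unadjusted test allows for this as noise; recording the entry status would allow it to be removed.

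**The case against.** **Kidney status at entry is not wholly missing.** This stands. Chronic kidney disease, the two severity scores and day-1 creatinine are collected, and a rise in creatinine can be followed in patients not on dialysis. A reader might infer that the trial can neither describe nor adjust for renal function at entry; the data list does not support that. The firm gap is ongoing renal replacement and AKIN stage.

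**The words after inclusion already point to new injury.** This stands as a statement of intent, so it would be wrong to assume that every entry case will be scored as an event. It does not settle existing injury that worsens, it is absent from the endpoint lists, and it is not attached to dialysis.

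**Dilution is not certain.** This stands. It depends on how entry cases are scored and which effect measure is used; scored as non-events, they leave the risk ratio unchanged. A reader might infer that any effect is pulled towards the null; the protocol fixes too little to support that.

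**Kidney injury is a safety matter here.** A reader might infer this, but the complications that the protocol attributes to the procedure do not include it.

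**The definition belongs in the analysis plan, and the values may be in the patient file.** The first half stands for the at-risk set and the rule for worsening. The second may be true, since routine data are kept in the file and the case report form itself is not shown. Even so, the Study assessment list is what the protocol asks sites to record, and it omits these two values.

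**Little would change.** On the assumed figures, power stays low even after restriction to patients at risk. The gain lies in interpretability more than in power.

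**Conclusion.** The point holds in limited form. AKIN stage and ongoing renal replacement at inclusion are not listed, although patients with either may enter and both kidney injury after inclusion and dialysis are outcomes. As written, new dialysis cannot be separated from existing dialysis, and new kidney injury depends on each open-label investigator's unchecked judgement.

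The size cannot be known from the protocol. What holds generally is that entry cases counted as events shrink the risk difference by the factor 1 − f if f is equal in the arms. Every percentage in the illustration rests on assumed injury rates and assumed values of f.

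Severity is minor. This is one of eight secondary endpoints in an exploratory pilot without a sample size calculation, and the primary endpoint is untouched.

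**What to change.** 1. In Study assessment, add two items to those recorded at inclusion: AKIN stage at inclusion, and renal replacement at inclusion (yes/no).
2. Count kidney injury as new, or as a rise of at least one AKIN stage above the inclusion stage, in patients not on renal replacement at inclusion. A patient entering at stage 3 cannot meet this definition and is best shown separately.
3. Count dialysis as newly started, in patients not on renal replacement at inclusion.
4. Add the restriction to after inclusion to both secondary endpoint lists (Synopsis and main text), so that they agree with Study assessment.

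The detail of items 2 and 3 may sit in the statistical analysis plan; item 1 has to be in the data collection.

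The cost is two case report form fields from routine records, a few lines of wording, and a smaller at-risk set for these two outcomes. No clinical management changes.
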